#### Health Care Resource Use Outcomes

Self-reported exacerbation, emergency department (ED) visit, and hospitalization data will be collected. South Western Sydney Local Health District’s electronic medical records will also be systematically reviewed to verify participant self-reports. Data will be updated at 6 and 12 months from MBC enrollment and will include the annual number of the following:

ED presentations (all presentations), lasting <24 hours, that do not result in hospitalization, as well as breathlessness-related ED presentations, lasting <24 hours, that do not result in hospitalizationUnplanned hospitalizations, including unplanned hospitalizations due to breathlessnessHospital length of stay in bed days (all unplanned hospitalizations), as well as breathlessness-related hospital bed daysExacerbations of COPD counted by patient-reported activation of COPD action plan, along with occasions of prescription of antibiotics and/or corticosteroid for the treatment of symptoms of respiratory exacerbation during hospitalized events

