#### Statistical Analysis Plan

Descriptive statistics will be applied to the study population to characterize them in terms of demographic and baseline clinical parameters. Normally distributed continuous variables will be expressed as mean (SD), nonparametric variables will be defined by median and range, while categorical variables will be expressed as percentages.

Breathlessness outcomes will be compared across 3 time points: baseline, 9 weeks, and 52 weeks using repeated measures ANOVA. Predictors of response will be sought using linear regression models with sex, forced expiratory volume (FEV) in 1 second, ratio of FEV to forced vital capacity, BMI, Montreal Cognitive Assessment, and baseline anxiety and depression scores as prespecified variables. Health care use measures and exacerbation data for the 12 months prior to MBC enrollment will be compared with the corresponding values for the 12 months after MBC enrollment, using Student 2-tailed *t* tests or nonparametric tests as appropriate. Protocol completer and dropout populations will be compared in terms of baseline characteristics (sex, age, FEV in 1 second, pack years, BMI, CRQ-Mastery subscale, CAT score, and Montreal Cognitive Assessment) to investigate potential selection bias.

Finally, comparison will be made with patients’ baseline data from the year prior to enrollment in the breathless clinic, benchmarked against nonparticipant comparator hospital deidentified patient medical records with (1) ED presentations for reasons of breathlessness, triaged as “shortness of breath—respiratory” or (2) hospitalized with exacerbations of COPD or heart failure as per diagnostic related group assignment. These benchmarking comparisons will use deidentified electronic medical records and will contribute to exploratory analyses undertaken to better understand the health care use of our sample cohort in the context of the overall health care use patterns of our local population “breathless” groups.

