Our study protocol excludes patients based on English language proficiency, which represents another important limitation. Ideally language should not prevent equitable access to medical care nor opportunities to participate in health research. The decision to include only English-speaking participants was made due to significant ethnic and cultural differences in the expression and description of breathlessness. Additionally, some of the outcome measures are only validated in English. The exclusion of people who do not speak English will limit the generalizability of our results to the English-speaking population. The authors estimate the impact of exclusion due to English proficiency to be small as shown in Figure 1, noting that exclusion percentages are estimates based on census data. The 2021 census data from the Australian Bureau of Statistics inform that the Macarthur and Wollondilly local government areas have, when compared with Sydney and New South Wales, a higher concentration of English-only speakers [22]. To mitigate the impact on generalizability and perhaps to provide an alternative means to characterize and express the severity of breathlessness in future iterations of the program, the Dalhousie pictorial scales, which help bypass literacy and language barriers, have been included as an outcome measure.

Finally, regarding COPD exacerbations, the authors recognize that patient recall of these events is notoriously poor, particularly for milder events, either self-treated or treated via primary care in the community. Moreover, Australia’s national guidelines, COPD-X, recommend that such patients have an exacerbation plan, along with prescriptions for relevant rescue medications making it even more complicated to establish the timing of these events. We will seek to confirm more severe events, resulting in an ED visit or hospitalization, systematically using local hospital electronic medical records. However, patient reports of exacerbation and health care use events will be sought nonetheless, given the possibility of capturing additional events occurring outside our health district, interstate, or within primary care, while acknowledging that the reporting and therefore capture of these events will be less reliable.

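### The exploratory benchmark sets participants, who need no prior event, against comparators selected for having had one, with no common event criterion and no stated counting rule for comparators

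*Protocol article*

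**What the plan says.** The benchmark is described in the last paragraph of the protocol article's Statistical Analysis Plan section. On the participant side, "comparison will be made with patients’ baseline data from the year prior to enrollment in the breathless clinic". That experience is "benchmarked against nonparticipant comparator hospital deidentified patient medical records with (1) ED presentations for reasons of breathlessness" (identified by a respiratory breathlessness triage category), or with patients "hospitalized with exacerbations of COPD or heart failure as per diagnostic related group assignment". The article adds: "These benchmarking comparisons will use deidentified electronic medical records and will contribute to exploratory analyses". The stated purpose is to view the cohort's health care use in the context of local breathless groups.

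Participants enter differently. The eligibility criteria require airflow obstruction on spirometry, an mMRC score of at least 2 and age of at least 40; none requires an earlier ED visit or admission. The Recruitment section allows referral from outpatient services or once stable after a COPD-related admission.

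Participant events are defined under Health Care Resource Use Outcomes. The ED measure is "ED presentations (all presentations), lasting <24 hours, that do not result in hospitalization", with a breathlessness-related subset. Admissions are all unplanned ones, also with a breathlessness-related subset. The source is self-report, and "electronic medical records will also be systematically reviewed to verify participant self-reports". Strengths and Limitations explains that self-reports are still sought, "given the possibility of capturing additional events occurring outside our health district, interstate, or within primary care".

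**The concern.** A comparator cannot have zero events of the type that brought the record in; a participant can. If yearly counts are compared over a window that includes the comparator's index event, the comparator mean is conditional on at least one event and the participant mean is not. Two groups with identical underlying rates would then show different means. The article states no matching, no shared event criterion and no conditioning that would remove this.

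There is a second, smaller problem. The participant ED measure leaves out visits that last 24 hours or more or end in admission, while the comparator ED entry criterion has no limit on length or outcome. The article does not say how events are counted once a comparator record is selected.

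At stake is the answer to the benchmark's own question: whether this cohort uses more or less care than other breathless patients in the district. A selection artefact could be read as a real difference in use.

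**Working it through.** The article gives no figure for the benchmark, so there is nothing to reproduce. The size of the selection effect is shown under assumptions.

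**Inputs.** From the article: comparators have at least one qualifying event; participants need none, but some are referred after an admission. Assumed, because the article does not give them: the yearly rate m (0.5 to 3, equal in both groups), the count distribution (Poisson, or negative binomial with size k), and the share s of participants who entered after a qualifying event.

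**Formulas.**
- Probability of no event: P0 = exp(−m) for Poisson; P0 = (1 + m/k)^(−k) for negative binomial.
- Comparator mean: T = m / (1 − P0).
- Participant mean: s·T + (1 − s)·m.
- Ratio = participant mean / T. With equal rates and like-for-like selection it would be 1.00.

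**Worked case, m = 1, Poisson.** P0 = exp(−1) = 0.368, so T = 1 / 0.632 = 1.58. With s = 0 the ratio is 1 / 1.58 = 0.63. With s = 0.5 the participant mean is 0.5 × 1.58 + 0.5 × 1 = 1.29, and the ratio is 1.29 / 1.58 = 0.82.

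**Range.**

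| m per year | Poisson T | ratio, s = 0 | ratio, s = 0.5 | NB (k = 0.5) T | ratio, s = 0 | ratio, s = 0.5 |
|---|---|---|---|---|---|---|
| 0.5 | 1.27 | 0.39 | 0.70 | 1.71 | 0.29 | 0.65 |
| 1 | 1.58 | 0.63 | 0.82 | 2.37 | 0.42 | 0.71 |
| 2 | 2.31 | 0.86 | 0.93 | 3.62 | 0.55 | 0.78 |
| 3 | 3.16 | 0.95 | 0.98 | 4.82 | 0.62 | 0.81 |

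The effect is largest when events are rare or concentrated in a few patients. It disappears at s = 1, or when both groups must have an event of the same type in the same window.

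**What would offset it.** With s = 0 and Poisson counts, participants look equal or higher once their true rate exceeds that of the comparators' source population by a factor of T/m: 2.54 at m = 0.5, 1.58 at m = 1 and 1.16 at m = 2.

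**Counting rule.** Suppose, as an assumption only, that comparator ED visits were counted whatever their outcome and that 20% to 60% of ED visits end in admission. The participant rule would then capture 0.8 to 0.4 of the same visits. If participants' all-cause visits were set against comparators' breathlessness visits, and 30% to 70% of visits were for breathlessness, the ratio (1 − admitted share) / breathlessness share runs from 0.4/0.7 = 0.57 to 0.8/0.3 = 2.67. A mismatch in counting could therefore act in either direction.

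**The case against.** A reader might infer that the article counts events by one definition in participants and by another in comparators. It does not say so. The triage category and the diagnostic group select comparator records; no counting rule for those records is given, and the participant measures could be applied to both groups. An article may leave such detail to a fuller document. What stands is that the participant ED measure and the comparator entry criterion do not match, so a common rule has to be chosen.

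A reader might also infer that participants are bound to look like lower users. That is too strong. Some are recruited after an admission and so are selected on an event too. All-cause counts and out-of-district self-reports push their numbers up. A cohort with moderate to severe COPD and an mMRC score of at least 2 may have a higher true rate than an ED group that need not have COPD.

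The truncation is also limited. The two comparator routes are alternatives, so entry by an ED visit does not force an admission, nor the reverse. Only the qualifying event type is affected, and only if the window contains the index event; the article states no comparator window.

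Finally, describing a cohort beside openly hospital-using groups is legitimate, and the analysis is labelled exploratory. This limits the consequence. It does not remove the difference in selection, which the article itself fixes.

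**Conclusion.** The point holds as a difference in selection with no common event criterion. At equal underlying rates, and with a window that includes the index event, it pulls participants towards lower apparent use: a ratio of about 0.63 at 1 event per year (Poisson, no participant selected on an event), or 0.82 if half entered after one. Every rate, dispersion value and share is an assumption, and the observed direction could be reversed by the offsetting factors above. Even then, the comparison would mix selection with use and could not be read as either.

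The data are from before enrollment, so neither the intervention effect nor the before-and-after tests of health care use depend on this benchmark. The harm is confined to a misleading account of how the cohort's use compares with that of local breathless patients. It is worth correcting because analysis is still under way.

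**What to change.** For this exploratory benchmark only:

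- Count events in both groups from the same district electronic records, over the same 12-month length, with one written rule for ED visits and one for admissions. For ED visits, say whether those of 24 hours or more, or ending in admission, are included, and apply that to both groups.
- Alongside the full cohort, add a comparison limited to participants with at least one event of the same qualifying type as the comparator group (ED visit or admission) in the same 12-month window.
- Report the share of participants with no qualifying event as a result in its own right.
- Label any full-cohort comparison as being against patients selected for an index event.

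The cost is a few sentences in the analysis plan and an extra query of records already under review. The matched comparison will include fewer participants, and events outside the district will be excluded on both sides. Keeping the full-cohort figures beside it means that low users are not lost from the description.

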#### Qualitative Outcomes

Patients and carers (where relevant) will undertake semistructured, audio-recorded interviews up to 9 weeks after completion of MBC. These interviews will explore participant perceptions of the MBC, any particularly helpful components, and seek recommendations for future versions of the service (Multimedia Appendix 1). To identify key concepts and themes, thematic analysis will be conducted [19]. Interviews will be coded by 2 researchers, one of whom has been involved in the conduct of the MBC and a researcher from the Westmead Breathlessness Service, to provide comprehensive assessment of the data. Input from additional researchers, experienced in qualitative methods, will provide triangulation of the results to enhance trustworthiness of the analysis. The qualitative data will complement the quantitative findings and offer a more complete understanding of the intervention’s effects.

## Results

Data collection commenced in March 2022, and recruitment is now complete, with 92 participants finishing the protocol by the end of March 2024. Data analysis is ongoing, and results are anticipated in early 2027. This project has been funded incrementally according to achievement of predefined milestones. The final milestone payment was received in October 2025.

## Discussion

### Anticipated Findings

This study adds to the literature by evaluating the change from baseline after a 9-week multidisciplinary, home-based health intervention to address the symptom of breathlessness in a cohort of Australian patients who have moderate to severe COPD. The study based on this protocol will provide important insights into applying this type of intervention to patients with COPD, a chronic disease. The authors anticipate that this study will help to inform models of care for patients with COPD enduring breathlessness as a persistent and distressing symptom, providing information about the potential durability of these interventions, and the characteristics of patients with COPD who might be most likely to benefit.

### Comparison With Prior Work

Breathlessness intervention services have been shown to be effective for breathlessness over the short term [7] The first examples of these services targeted patients with malignant disease, using complex, multicomponent, nonpharmacological interventions for the management of breathlessness [20]. Subsequent trials enrolled heterogeneous populations of patients with a mixture of malignant and nonmalignant diseases, including some patients with COPD. The authors are aware of a recently completed randomized controlled trial in Australia targeting a population of patients with COPD using a breathlessness intervention model similar to our own. Breathlessness in COPD often remains persistent and distressing despite best pharmacological treatments. However, COPD is a chronic disease, and so patients may live for many years with this burden. For these patients, not only are effective treatment strategies needed but benefit must be sustained over the long term. The proposed protocol uses a multidisciplinary home-based complex health service intervention similar in type to those known to confer significant short-term benefits for breathless patients in mixed disease populations, aiming to confirm its applicability to breathless patients with COPD, and also exploring the durability of benefits and best selection of patients.

### Strengths and Limitations

The study’s focus on a homogeneous disease population of patients with moderate to severe COPD will ensure that the results are highly relevant to this specific group. This targeted approach will allow for more precise conclusions regarding the usefulness in this cohort of the intervention being tested. That said, we will recruit a wide range of patients with COPD in terms of severity and exacerbation susceptibility, ensuring broad applicability to this important, and large, patient group. Thus, our results will complement the existing evidence base, as most previously published data include more heterogeneous participant populations; patients with malignant disease, and/or patients with a variety of restrictive and obstructive nonmalignant respiratory disease.

To our knowledge this is the first long-term study protocol for this type of intervention service. By spanning a longer period, an entire year, the study will mitigate the potential confounding effects of seasonal variations in COPD symptoms and exacerbations. This will ensure that the observed outcomes are more likely attributable to the intervention rather than external seasonal factors. Additionally, the proposed intervention requires behavior change, which can take time to implement. By having a longer duration than previous interventions, we hope to enable patients to embed into their routine the suggested nonpharmacological strategies and to thus realize a durable effect beyond the 9 weeks of the program.

The 12-month follow-up period will also provide insight into the durability of the intervention response over a prolonged period. To date, the scientific literature contains few reports of outcomes for this type of intervention extending beyond 2 or 3 months. Showing sustained symptomatic benefits for this type of population with nonmalignant, chronic disease is perhaps much more important than demonstrating a short-term response.

Finally, the use of the CAT as a key assessment tool will underscore the study’s relevance to clinical practice. The CAT is a validated, disease-specific instrument that provides a comprehensive evaluation of COPD symptoms and their impact on patients’ quality of life. This may allow for the MBC to be ranked against other treatment interventions used in COPD, so that any positive study findings can be integrated into existing treatment paradigms, thereby facilitating the translation of research into practice.

However, this study has several limitations that must be acknowledged. First and foremost is the nonrandomized study design; all recruited participants will receive the intervention and act as their own controls. This design could introduce both time and attrition bias and is a clear limitation on the level of evidence produced. The authors were aware of a randomized controlled trial [8] underway in another Australian center using a similar model to our protocol, and we therefore chose a nonrandomized study design to address clinical need while still demonstrating translatability to a different population and setting. Given that COPD is a chronic and progressive disease, evaluating the impact of breathlessness over time may still yield valuable insights, provided the results are interpreted carefully. While potential mortality among participants with more severe disease may skew study results, on the other hand, worsening disease trajectory may mask benefits when determining results over the longer term. Considering this, even if patients appear to be stable with respect to outcome measures at 12 months, this may actually represent improvement compared with the expected trajectory in COPD, which is one of deterioration. In fact, clinically significant breathlessness is a known marker of poor prognosis for patients with COPD [21], and so our target population will be expected to deteriorate more rapidly than the COPD group as a whole.

The study’s proposed setting, a single metropolitan center situated within a large semirural area, may limit the general applicability of our results. However, the authors are aware of concurrent research on this topic being conducted at other centers and health districts throughout Australia, which should help to address this.

Our study protocol excludes patients based on English language proficiency, which represents another important limitation. Ideally language should not prevent equitable access to medical care nor opportunities to participate in health research. The decision to include only English-speaking participants was made due to significant ethnic and cultural differences in the expression and description of breathlessness. Additionally, some of the outcome measures are only validated in English. The exclusion of people who do not speak English will limit the generalizability of our results to the English-speaking population. The authors estimate the impact of exclusion due to English proficiency to be small as shown in Figure 1, noting that exclusion percentages are estimates based on census data. The 2021 census data from the Australian Bureau of Statistics inform that the Macarthur and Wollondilly local government areas have, when compared with Sydney and New South Wales, a higher concentration of English-only speakers [22]. To mitigate the impact on generalizability and perhaps to provide an alternative means to characterize and express the severity of breathlessness in future iterations of the program, the Dalhousie pictorial scales, which help bypass literacy and language barriers, have been included as an outcome measure.

Finally, regarding COPD exacerbations, the authors recognize that patient recall of these events is notoriously poor, particularly for milder events, either self-treated or treated via primary care in the community. Moreover, Australia’s national guidelines, COPD-X, recommend that such patients have an exacerbation plan, along with prescriptions for relevant rescue medications making it even more complicated to establish the timing of these events. We will seek to confirm more severe events, resulting in an ED visit or hospitalization, systematically using local hospital electronic medical records. However, patient reports of exacerbation and health care use events will be sought nonetheless, given the possibility of capturing additional events occurring outside our health district, interstate, or within primary care, while acknowledging that the reporting and therefore capture of these events will be less reliable.

